 **H2.**
*IST increases the acceptance of strength training by older adults.*

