## 2. Methodology

### 2.1. Design of the Intervention Study

This non-randomised, single-group, pre-post-intervention, exploratory trial will evaluate the impact of IST on sarcopenia and dynapenia in adults over 70 years of age across a 16-week period. A detailed timeline of enrolment, interventions, and assessments is presented in Table 1. Each participant will act as their own control, comparing their baseline and post-intervention status. A concurrent comparison group will not be included in this phase, which will focus on feasibility and preliminary effects (see Section 4 for a discussion of limitations). Allocation to different intervention groups is not applicable. The study aims to measure the effectiveness of IST in improving muscle mass, strength and quality of life, as well as its practical applicability. Participants will be recruited in Vitoria (Alava) and Zamudio (Bizkaia, Spain) through Baigene S.L., the Judizmendi Civic Centre (Vitoria-Gasteiz City Council) and the Estadio Vital Fundazioa Foundation.

**Table 1 healthcare-13-01573-t001:** Timeline for Study Participation.

Study Phase	Main Activities	Approximate Timing
Recruitment	Identification of potential participants, initial contact through the collaborating organisations (BAIGENE S.L., Judizmendi Civic Centre, Fundación Estadio Vital Fundazioa).	Prior to the start of the study
	1st Meeting (Information and Consent): Detailed explanation of the study, objectives, exercises; signing of the informed consent form.	Approx. 2–3 weeks before baseline assessment
	2nd Meeting (Criteria Evaluation): Questionnaire (sociodemographic, habits, pathologies, medication); Comprehensive Geriatric Assessment (CGA); Review of analytical data; Anthropometric measurements and Body Composition (height, weight, BMI, InBody for SMM/ASMM); Diagnostic tests for sarcopenia (gait speed, grip strength, and confirmation of low muscle mass with ASMM/ASMI) according to EWGSOP criteria.	Approx. 1–2 weeks before baseline assessment
Baseline Assessment	(Pre-Intervention Assessment): Measurement of physiological variables (BP, HR, SpO2), functional capacity (MVIC of 8 muscle groups, static posture), quality of life (EQ-5D-5L), saliva sampling for genetic analysis.	Week 0 (one week before the start of the IST)
Intervention	IST Programme: 2 sessions/week, 30 min/session, supervised. Progression according to Table 2	Weeks 1 to 16

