1.Other Indicators of Sarcopenia and Dynapenia:○Handgrip Strength: Specific measurement variable: Maximal handgrip strength, measured in kilograms (kg) (Jamar Dynamometer). Analysis metric: Absolute change from baseline to week 17. Method of aggregation: Mean and SD. Time point(s): Baseline (week 0) and post-intervention (week 17). Clinical Relevance: A component of the sarcopenia diagnosis and a predictor of functionality and mortality.○Gait Speed: Specific measurement variable: Usual gait speed over a 4 m course, measured in meters/second (m/s) (Newtest Powertimer). Analysis metric: Absolute change from baseline to week 17. Method of aggregation: Mean and SD. Time point(s): Baseline (week 0) and post-intervention (week 17). Clinical Relevance: A measure of physical performance, a component of the sarcopenia diagnosis, and a predictor of adverse outcomes.○MVIC of other muscle groups: Specific measurement variable: MVIC for the peck deck, pull over, lateral shoulder elevation, leg curl, low back, hip abduction and hip adduction, measured in Newtons (N) (CIEX SYSTEM). Analysis metric: Absolute change from baseline to week 17. Method of aggregation: Mean and SD of the change per exercise. Time point(s): Baseline (week 0) and post-intervention (week 17). Clinical Relevance: Assesses the training response across different body regions.○Sarcopenia Status: Specific measurement variable: Diagnostic status of sarcopenia according to EWGSOP2 criteria (based on muscle strength, muscle mass, and physical performance). Analysis metric: Change in the proportion of participants meeting the diagnostic criteria from baseline to week 17. Method of aggregation: Frequencies and percentages. Time point(s): Baseline (week 0) and post-intervention (week 17). Clinical Relevance: Quantifies the overall impact of the intervention on the diagnostic status of the condition.2.Health-Related Quality of Life (HRQoL):○Specific measurement variable: The index score derived from the EQ-5D-5L descriptive system and the Visual Analogue Scale (VAS) score of the same questionnaire. Analysis metric: absolute change from baseline to week 17 for both the index score and the VAS score. Method of aggregation: Mean and SD of the changes. Time point(s): Baseline (week 0) and post-intervention (week 17). Clinical Relevance: Measures the overall self-perceived health and the impact of the intervention on multiple dimensions of participant well-being.3.Applicability of the IST Protocol:○Perceived Safety: Specific measurement variable: Score on a 5-point Likert scale for perceived safety. Analysis metric: Mean score post-intervention. Method of aggregation: Mean and SD. Time point(s): Post-intervention (week 17). Relevance: Assesses the participant’s subjective perception of safety, providing data to test hypothesis H1.○Acceptance/Satisfaction: Specific measurement variable: (1) Adherence rate (% of completed sessions); (2) Score on a 5-point Likert scale for overall satisfaction. Analysis metric: Percentage for adherence; Mean score post-intervention for satisfaction. Method of aggregation: Percentage for adherence; Mean and SD for satisfaction score. Time point(s): Adherence monitored continuously during the intervention (weeks 1–16); Satisfaction assessed post-intervention (week 17). Relevance: Measures the feasibility and appeal of the intervention to participants, providing data to test hypothesis H2.○Perceived Difficulty: Specific measurement variable: Score on a 5-point Likert scale for perceived difficulty. Analysis metric: Mean score post-intervention. Method of aggregation: Mean and SD. Time point(s): Post-intervention (week 17). Relevance: Evaluates the perception of technical simplicity, providing data to test hypothesis H3.○Adverse events: Specific measurement variable: Incidence, type, severity and causality (relationship to IST). Analysis metric: Frequencies and descriptive summary. Method of aggregation: Counts and percentages. Time point(s): Monitored continuously during the intervention period (weeks 1–16). Relevance: Assesses the objective safety profile of the protocol, providing data to test hypothesis H1.

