#### 2.2.2. Pre-Intervention Assessment

One week before starting the 16-week IST, a comprehensive baseline assessment will be performed on the selected subjects to collect baseline data. This assessment, conducted by a physical activity professional and the research group doctor, will allow for detailed monitoring and accurate assessment of the effects of the programme, including the following variables:Physiological Variables: BP and heart rate HR (Omron M3 Comfort^®^ blood pressure monitor, HEM-7134-E, Omron Healthcare Co., Kyoto, Japan) and O2 saturation (OXYM4000 pulse oximeter, Quirumed S.L.U., Valencia, Spain) will be measured. Three resting measurements will be taken per participant, using the mean as the final data.Functional Capacity:○MVIC: The MVIC of each muscle group of the IST programme will be assessed at individualised intermediate angles (determined according to anatomical structure and motor restrictions, recorded with a HALO© digital goniometer). The CIEX SYSTEM machine (Ciex Systems©, Durango, Spain) with sensors and Chronojump software (Chronojump Boscosystems^®^, Barcelona, Spain) will be used for instantaneous measurement and visualisation of strength, tools also used in all IST sessions and for monitoring purposes.○Static Posture Assessment: Participants will be photographed in anatomical position (frontal and sagittal planes) with a Casio Exilim Pro EX-F1 camera (configuration: level tripod, lens at umbilical height, at 4 m, optical zoom, aperture priority, focal length 50 mm, f5.6, ISO 200) [81]. An analysis of documented validity and reliability for postural analysis will be performed with Kinovea^®^ software (v.0.9.x+) [82,83]. Adhesive markers or direct image identification may be used for key anatomical points [84] (sagittal: tragus, C7, acromion, greater trochanter, lateral femoral epicondyle, peroneal malleolus; frontal: acromions, anterior superior iliac spine (ASIS), posterior superior iliac spine (PSIS), patellar centre, tibial malleoli). Postural parameters will be calculated from these points (sagittal: head-neck alignment (HNA) [82], shoulder alignment, estimated spinal curvatures, pelvic tilt [84], knee alignment; frontal: head tilt/symmetry, shoulder height, pelvic symmetry [81], lower limb alignment [82]). Angles (degrees) and distances (cm/mm, after calibration if size reference is used) shall be recorded. Pre-post change will be an outcome of interest. Image analysis shall be performed, if possible, by a blinded assessor (see Section 2.1.3) [83].HRQoL: The EuroQol EQ-5D-5L questionnaire (5 items, 5 dimensions, 5 response levels) will be used [85,86]. This instrument includes two parts: a descriptive system comprising five dimensions (mobility, self-care, usual activities, pain/discomfort, anxiety/depression), each with five response levels, and a VAS where participants rate their overall health.Applicability of the IST Protocol (scales administered post-intervention):○Safety (H1): Assessed by: (1) Analysis of Adverse Events (AEs) (incidence, type, severity, relationship to IST) over 16 weeks (procedures detailed in Section 2.4.3); ‘low risk’ if the incidence of IST injuries is minimal. (2) Perceived Safety: 5-point Likert scale (1 = extremely unsafe, 5 = extremely safe) post-programme, with face validity and based on similar approaches [87]; a mean score ≥ 4 will be expected.○Acceptability (H2): Assessed by compliance rates (≥90% sessions) and overall satisfaction (5-point Likert scale: 1 = extremely dissatisfied, 5 = extremely satisfied) post-programme, using validated measures [88]; a mean satisfaction score ≥ 4 will be expected.○Difficulty (H3): Assessed with a 5-point Likert scale on perceived challenge (1 = not challenging at all, 5 = extremely challenging) post-programme, validated approach [89]; a mean score ≤ 2 will be expected.Genetic Analysis: Saliva samples will be collected using buccal swabs (4N6FLOQSwab, Life Technologies, Waltham, MA, USA). DNA will be extracted from these samples (QIAmp DNA Mini kit, Qiagen, Venlo, The Netherlands) and subsequently quantified (Qubit, Life Technologies). Genetic polymorphisms, specifically Single Nucleotide Polymorphisms (SNPs) and Insertions/Deletions (INDELs), will be analysed in genes associated with the response to strength training, hypertrophy, and strength gains [63,64,65,66,67,68,69,71,72,73]. Specifically, genes linked to the following will be analysed:○Muscle fibre typology: such as ACTN3 (R variant associated with a higher proportion of type II fibres, crucial for strength/power and affected by sarcopenia/dynapenia in ageing) [63,64].○Response to training: including ACE [63,65,66], NRF2, CKMM, MCT1, AMPD1, and the co-activators PPARGC1A and PPARGC1B (involved in mitochondrial biogenesis and exercise adaptation).○Muscle fibre damage and regeneration: genes such as IGF2, MLCK, CASP [72], MMP3 [72], TNC and GDF5 [73], which influence the response to exercise microtrauma and its repair. Moderate exercise-induced muscle damage (EIMD), potentially triggered by IST at long angles, is considered to contribute to remodelling and adaptation.○Vascularisation: NOS3 and VEGFA [67,69], essential for oxygen/nutrient supply, muscle growth and recovery, optimising metabolic stress and hypertrophic response.○Inflammation: TNF-α, CRP [60], IL-6 [60] and IL6-R, which are relevant because inflammation contributes to sarcopenia and modulates the anabolic response [70].○Oxidative damage response capacity: SOD2 [71], CAT and GPX, crucial for muscle recovery and adaptation to training stress.○Fat and carbohydrate metabolism (nutrigenomic factors): Polymorphisms in FABP2, ADRB2, ADRB3, FAT/CD36, UCP2, GCKR, ADCY5 and GIPR, which may influence nutrient uptake and hypertrophic response [74,75,76].

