#### 2.2.3. Post-Intervention Evaluation

A final assessment will be performed one week after completion of the 16-week IST programme (week 17). All baseline measurements (physiological variables, functional capacity including MVIC and posture, quality of life by EQ-5D-5L, and the components of the sarcopenia diagnosis) will be repeated to assess any changes induced by the training, with the exception of the genetic analysis, which is only performed at baseline. Additionally, applicability questionnaires (safety, acceptance and perceived difficulty using Likert scales) [87] will be administered to assess the IST protocol.

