#### 2.3.2. Analysis Strategy

Primary and secondary quantitative variables will be compared pre-post with Student’s *t*-tests for related samples, after testing for normality (Shapiro-Wilk). If the data are not normally distributed or contain outliers, non-parametric tests (e.g., the Wilcoxon signed-rank test) will be employed. Effect sizes (Cohen’s d) and confidence intervals will be calculated. Multivariate analyses will include a multiple linear regression to explore the influence of genetic and environmental variables on strength and muscle mass improvement, with Bonferroni correction for genetic analyses. Qualitative variables (e.g., sarcopenia diagnosis) will be analysed by using McNemar tests. Applicability variables (Likert scales, adverse events) will be analysed with descriptive statistics and *t*-tests or Wilcoxon tests for pre-post comparisons on Likert scales. Additionally, exploratory subgroup analyses will be performed to assess whether the response to IST on primary variables differs according to sex, age ranges (70–79 vs. ≥80 years) and baseline severity of sarcopenia/dynapenia. Adjustment for baseline covariates will be considered in regression models. The software will be IBM SPSS v29.0 and R v4.3.1.

For the assessment of the secondary hypotheses concerning the applicability (Section 2.2.2) of the IST protocol, specific analyses will be carried out:

Hypothesis H1 (low injury risk): This will be assessed through two approaches. First, Adverse Events (AEs) will be recorded (including their type, severity, and causality), and ‘low risk’ will be inferred if the incidence of IST-related injuries is minimal and comparable to or lower than rates reported in the literature for strength training in older adults [1,33,34,35]. Second, Perceived Safety will be measured post-intervention using a 5-point Likert scale; the approach for this subjective scale is based on similar methods used in previous research [87]. The hypothesis will be supported by a mean score of ≥4.

Hypothesis H2 (high acceptance): This will be assessed by: (1) compliance rate, with a success threshold of ≥90% of completed sessions, and (2) a satisfaction score from a 5-point Likert scale administered post-intervention, using a validated measurement approach [88]. The hypothesis will be supported by a mean satisfaction score of ≥4.

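### H2 is worded as an increase in acceptance, but its measures and success rule test only a level reached with training, so an increase cannot be told apart from no change

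*Protocol article*

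**What the plan says.** The list of secondary hypotheses in Section 1 gives H2 as "IST increases the acceptance of strength training by older adults".

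Section 2.2.1 names two measures for it, the percentage of sessions completed and a 5-point satisfaction score, with this timing: "Adherence monitored continuously during the intervention (weeks 1–16); Satisfaction assessed post-intervention (week 17"). Section 2.2.2 lists the scales under the baseline visit but marks them "Applicability of the IST Protocol (scales administered post-intervention"). Section 2.2.3 places them at the final visit: "Additionally, applicability questionnaires (safety, acceptance and perceived difficulty using Likert scales) [87] will be administered to assess the IST protocol". Table 1 agrees, and its week 0 row contains no acceptance item.

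On the design, Section 2.1 says: "A concurrent comparison group will not be included in this phase".

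The decision rule is in Section 2.3.2. It opens with "Hypothesis H2 (high acceptance): This will be assessed by: (1) compliance rate, with a success threshold of ≥90% of completed sessions", adds the satisfaction score as the second element, and ends: "The hypothesis will be supported by a mean satisfaction score of ≥4". The same section plans paired tests of Likert scales before and after training, and closes by promising a Cohen's d for the size of change in the Likert outcomes of H1 to H3.

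**The concern.** H2 is a statement about change. To show a change, the trial needs a value before training or a group that did not train, and it has neither for acceptance. What it will have is a level: how satisfied participants are at week 17 and how many sessions they attended. The object shifts too. H2 speaks of strength training in general, while the measures concern this IST programme.

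A report that follows the plan could therefore state that H2, as worded in Section 1, was supported, and readers would take this as evidence that IST raised older adults' willingness to do strength training. The data would show only that people who agreed to take part were content with the programme. H1 and H3 do not have this problem: they claim low injury risk and perceived simplicity, which are levels, and they are judged against levels.

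**Working it through.** **The plan's own figure.** H2 has no sample-size basis. The only derived number is for the knee-extensor outcome, and it supplies the n used below. For a paired t-test with d = 0.80 and two-sided α = 0.05, the noncentrality at n = 15 is 0.80 × √15 = 3.10. Exact power from the noncentral t distribution is 0.821, and 15 is the smallest n that reaches 0.80. With 15% losses, 15 / 0.85 = 17.6, hence 18. Both stated figures reproduce.

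**What each H2 measure can show.**

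| | Satisfaction | Adherence |
|---|---|---|
| Value before training | none | none (exists only in weeks 1–16) |
| Comparator | none | none |
| Criterion | mean ≥ 4 on a 1–5 scale | ≥ 90% of sessions |
| Type of criterion | absolute level | absolute level |

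No term in either criterion is a difference, so neither can respond to change as such.

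**Selection behind the adherence criterion.** Two sessions a week for 16 weeks is 32 sessions. 0.90 × 32 = 28.8, so 29 sessions are needed (29/32 = 90.6%; 28/32 = 87.5% falls short). The same 90% appears twice more. Under the exclusion criteria in Section 2.1.1, people who cannot commit to it are not enrolled. Under the withdrawal criteria in Section 2.1.2, falling below it after any extension is a ground for discontinuation. H2 is thus partly judged against the trial's own entry and retention standard. Section 2.1.3 encourages those who stop to attend week 17 where feasible, which reduces this selection but does not remove it.

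**How often the satisfaction criterion is met when nothing has changed.** Suppose each participant's acceptance is the same before and after training. The rule depends only on the true post-training mean m, the SD and n:

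P(observed mean ≥ 4) = 1 − Φ((4 − m) / (SD / √n)).

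The protocol gives neither m nor SD, so both are assumptions. Worked example: n = 18, m = 4.2, SD = 0.8 gives a standard error of 0.8 / √18 = 0.189, z = (4 − 4.2) / 0.189 = −1.06, and P = 0.856.

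| True mean m | n = 18, SD 0.6 / 0.8 / 1.0 | n = 15, SD 0.6 / 0.8 / 1.0 |
|---|---|---|
| 3.8 | 0.079 / 0.144 / 0.198 | 0.098 / 0.166 / 0.219 |
| 4.0 | 0.50 / 0.50 / 0.50 | 0.50 / 0.50 / 0.50 |
| 4.2 | 0.921 / 0.856 / 0.802 | 0.902 / 0.834 / 0.781 |
| 4.5 | 1.000 / 0.996 / 0.983 | 0.999 / 0.992 / 0.974 |

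A simulation with whole-number ratings gives the same picture. With 5%, 20%, 50% and 25% of ratings at 2, 3, 4 and 5 (mean 3.95), the criterion is met in 46% of trials of 18. With 10%, 50% and 40% at 3, 4 and 5 (mean 4.30), it is met in 98%.

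These figures concern satisfaction alone. If adherence must be met as well, they are upper limits for the full rule.

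**The change analyses.** A paired test and a Cohen's d of change each need two values per person. Sections 2.2.1, 2.2.2 and 2.2.3 provide one.

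**The case against.** The best reply is that this is one verb. *Increases* stands only in the one-line hypothesis. The objectives, the outcome definitions and Section 2.2.2 speak of acceptability, and Section 2.3.2 itself labels H2 as high acceptance. The trial is declared exploratory and focused on feasibility, and Section 4 concedes that without a control group changes cannot be attributed to IST with certainty. No primary outcome, sample size or safety rule depends on H2. All of this is right, and it makes the repair small. It does not remove the mismatch, because Section 2.3.2 still declares the hypothesis supported. Section 4 discusses how to attribute a change, whereas for acceptance no change is measured at all.

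A second reply is that the plan does foresee pre-post Likert comparisons. It does, but that text conflicts with the collection schedule and provides no baseline. The document contradicts itself here.

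A reader might infer more: that H2 would come out supported even if IST lowered acceptance. The documents do not support that. A programme that put participants off would be expected to produce missed sessions and low ratings, so either criterion could fail. What stands is the narrower point about increase versus no change.

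**Conclusion.** The point holds as a mismatch between a claim of change and a test of level. With no baseline and no comparator for acceptance, an increase cannot be estimated, and the rule gives the same answer for an increase as for a stable level of the same height. With zero true change, the satisfaction criterion is met with a probability from about 8% to nearly 100% as the true mean runs from 3.8 to 4.5. That range rests on assumed means, an assumed SD of 0.6–1.0, n = 18 and a normal approximation. The conclusion about wording and timing rests on none of these.

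Section 2.3.2 does not say outright whether adherence is required jointly with satisfaction, since its closing sentence names satisfaction only. The finding is the same on either reading.

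A reader might also infer that one acceptance item at week 0 would rescue *increases*. It would not: a paired change in an uncontrolled group of consenting volunteers still would not show that IST raises acceptance among older adults. Nor do the documents show that uptake counts are already planned. The recruitment text says only that recruitment will be monitored.

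The matter is confined to a secondary hypothesis, but its planned conclusion cannot follow from its data and should be corrected before reporting.

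**What to change.** 1. Reword H2 in Section 1 as the level claim that Section 2.3.2 already uses, for example: *IST is well accepted by participating older adults with sarcopenia.* Limit the conclusion on H2 to that statement. The outcome definitions in Sections 2.2.1 and 2.2.2 do not contain the claim of increase and need no rewording for this purpose.
2. In Section 2.3.2, remove the pre-post tests on Likert scales and the Cohen's d of change for H1 to H3. Report the post-intervention mean with a confidence interval for each scale instead.

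The cost is a few lines of text. No visit, instrument or participant is added. The downside is that the claim becomes less ambitious.
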